### Statistical analysis

Different general linear models (GLM) in SPSS will be used to analyze the main parameters. For instance, analyzing the empathy and aggression outcome (empathy ratings and b responses in the PSAP task), the outcome variables will be handled as the dependent variables. In addition, the group variable (active versus sham) will be used as the independent between-group variable, whereas the pre-post time will be included as a within-subject independent variable. A mixed design will be used in which the pre-post intervention in the experimental group will be compared with the pre-post intervention aggression outcomes in the sham group. The mixed design will be used for the PSAP outcomes, empathy ratings, self-report questionnaires, and assessment of risk of violence with the HKT-R instrument.

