##### Primary objective

The primary objective is to investigate tDCS as a new intervention to increase empathy and reduce violent behavior in offenders with substance abuse problems. This will be measured using the results of the empathy and aggression task from pre-test to post-test. In addition, we will study whether electrophysiological responses in the brain are affected by tDCS; this will be demonstrated through comparing the EEG from pre-test to post-test. We will use a mixed design to test whether event-related potential (ERP) amplitudes pre-post intervention differ between the active and sham group.

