### Power analysis

The sample size is based on the primary outcome and other studies from the aforementioned guidelines [76] and seen as achievable. The sample size is based on research [100] that reported large effect sizes (i.e. partial eta squared 0.25 and 0.21) for the active versus sham condition, using 15 participants per condition for three conditions. Because we have two experimental conditions but also include covariates, a sample size of 50 subjects (25 per condition) is considered to have enough power to detect an effect, when power is set to 80% and alpha of 5%, two sided.

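### The group-by-time test is a change-score test; adjusting each post-test for its own pre-test is at least as precise, by an amount set by the unstated pre-post correlation

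*Protocol article*

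**What the plan says.** The Statistical analysis section specifies general linear models with group (active or sham) as the between-subject factor, and "the pre-post time will be included as a within-subject independent variable". The contrast is the pre-post change in the active arm against the pre-post change in the sham arm. The scope is wide: "The mixed design will be used for the PSAP outcomes, empathy ratings, self-report questionnaires, and assessment of risk of violence". For the EEG outcome, the Primary objective section says the same: "We will use a mixed design to test whether event-related potential (ERP) amplitudes pre-post intervention differ between the active and sham group".

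The Power analysis section mentions covariates, but only as a consideration for sample size: "Because we have two experimental conditions but also include covariates". It names none, and nowhere does the article say that an outcome's own pre-test value is one of them. The article gives no pre-post correlation for any outcome.

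**The concern.** In a randomised trial the pre-test is known before treatment starts and is usually the best available predictor of the post-test. A change score subtracts the whole pre-test value, as if the slope of post on pre were 1. When r is below 1 and the SDs are similar, that over-corrects and adds noise. A regression estimates the slope and removes only what the pre-test actually predicts.

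With 25 patients per arm, precision is scarce. The Discussion expects the active control to shrink the effect relative to a no-treatment comparison, and names retention as the main challenge. If the true effect is smaller than the large effects used for planning, a loss of precision could decide whether the result is informative. The pre-tests are already scheduled, so nothing new has to be measured.

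**Working it through.** **1. The plan's own sample size.** Inputs from the Power analysis section: "large effect sizes (i.e. partial eta squared 0.25 and 0.21) for the active versus sham condition", a source study "using 15 participants per condition for three conditions", and "when power is set to 80% and alpha of 5%, two sided". Cohen's f = sqrt(eta²/(1 − eta²)), which is 0.577 for 0.25 and 0.516 for 0.21. For two equal groups d = 2f = 1.155 and 1.031. By the noncentral F distribution with two groups, 80% power needs 26 or 32 patients in total; with three groups it needs 33 or 40. Adding three or five covariates raises the two-group totals by at most one. No variant tried gives 50. With 50 patients the two-group power is 97.9% or 94.7%, so 80% is met as a floor.

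**2. Detectable effect at 50 patients.** The smallest standardised difference with 80% power is d = 0.81 (partial eta squared 0.14), in SD units of the score analysed.

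**3. Equivalence of the two tests.** On simulated data for 50 patients, the group-by-time t from the repeated-measures model and the t-test on change scores were both 0.20945, with 48 degrees of freedom.

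**4. Variances.** Let s1 and s2 be the pre and post SDs.

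- Change score: s1² + s2² − 2·r·s1·s2.
- Post-test adjusted for pre-test: s2²(1 − r²).
- Excess of the first over the second: (s1 − r·s2)², which is never negative.

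With s1 = s2 = 1 (an assumption) these become 2(1 − r) and 1 − r², with ratio 2/(1 + r). The equivalent number of patients is 50 × 2/(1 + r). Estimating the slope multiplies the adjusted variance by 1 + 1/(50 − 4) = 1.022.

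The detectable difference in outcome SDs is 0.809 × sqrt(2(1 − r)) for the change score. Multiplying by sqrt((1 + r)/2) gives the adjusted value, before the slope cost.

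| r (assumed) | Change variance | Adjusted variance | Ratio | Equivalent N | After slope cost | Detectable, change | Detectable, adjusted |
|---|---|---|---|---|---|---|---|
| 0.3 | 1.40 | 0.91 | 1.54 | 76.9 | 75.3 | 0.96 | 0.77 |
| 0.5 | 1.00 | 0.75 | 1.33 | 66.7 | 65.2 | 0.81 | 0.70 |
| 0.7 | 0.60 | 0.51 | 1.18 | 58.8 | 57.6 | 0.63 | 0.58 |
| 0.8 | 0.40 | 0.36 | 1.11 | 55.6 | 54.4 | 0.51 | 0.49 |
| 0.9 | 0.20 | 0.19 | 1.05 | 52.6 | 51.5 | 0.36 | 0.35 |

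At r = 0.5 the slope cost moves 0.70 to 0.70 × sqrt(1.022) = 0.71.

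**5. Simulation (10,000 runs per setting, 25 per arm).** Under no effect, both tests rejected in 4.9% to 5.3% of runs. With the effect set so that the change-score test has about 80% power, the adjusted model rejected in 90% of runs against 81% (r = 0.5), and in 85% against 80% (r = 0.7). The calculated adjusted power was 89.2% and 85.2%.

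**The case against.** The strongest reply is that nothing here is wrong. The planned contrast is a legitimate randomised comparison, its error rate holds, and at the article's own effect sizes 50 patients exceed 80% power. All of that stands. A reader might infer that the trial is underpowered, or that it lacks the 9 to 17 patients gained at r = 0.7 to 0.5. The documents do not support that: no stated target is missed, and r is not given.

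Second, the unnamed covariates might include the pre-test value. If so, the interaction test would already equal the baseline-adjusted analysis, and only the wording would need attention. An article may leave the covariate list to a fuller document. But this article does fix the role of the pre-test, as a level of the time factor, and it offers covariates as a reason for more patients rather than as a gain in precision.

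Third, the gain is uneven. Several instruments measure traits, past behaviour or historical indicators (SRP-SF, BIS-11, RPQ, HKT-R). A high correlation is plausible for these, and the gain could then be only a few patients.

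Two further inferences should be resisted. A mixed-design table also prints group and time main effects, but the article names the between-arm comparison of change as its contrast and does not propose to read main effects as treatment effects. Chance baseline imbalance can shift a change score through regression to the mean: its standard error is sqrt(2/25) = 0.28 SD, so a one-standard-error imbalance shifts the estimate by (1 − 0.5) × 0.28 = 0.14 SD at r = 0.5. Over randomisations this is not bias. It is largely the variance loss already counted above, not a second defect.

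**Conclusion.** The point holds as one of efficiency, not validity. For any outcome with one pre and one post value, the planned test is a change-score test, and adjustment for the pre-test is at least as precise apart from the small cost of estimating the slope. With equal SDs, the change-score variance exceeds the adjusted variance by 54% at r = 0.3, 33% at r = 0.5, 18% at r = 0.7 and 5% at r = 0.9. The direction does not depend on equal SDs; the size does, and r is an assumption throughout. The gain matters most if the true effect is smaller than the large effects used for planning.

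**What to change.** Before unblinding, name as the primary analysis of each outcome that has a pre-test a model of the post-test on arm plus that outcome's own pre-test value. Report the adjusted active-minus-sham difference with its 95% CI, and keep the group-by-time test as a sensitivity analysis. Apply this to the ERP amplitudes as well. State whether the covariates in the Power analysis section include the pre-test value, and name any others.

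The cost is one degree of freedom, about 2% of variance, and a documented, dated change to the analysis plan, since recruitment has begun. No extra patients, visits or measurements are needed, and SPSS general linear models fit the analysis.

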### Power analysis

The sample size is based on the primary outcome and other studies from the aforementioned guidelines [76] and seen as achievable. The sample size is based on research [100] that reported large effect sizes (i.e. partial eta squared 0.25 and 0.21) for the active versus sham condition, using 15 participants per condition for three conditions. Because we have two experimental conditions but also include covariates, a sample size of 50 subjects (25 per condition) is considered to have enough power to detect an effect, when power is set to 80% and alpha of 5%, two sided.

## Discussion

This study protocol describes the design of an intervention with multichannel tDCS targeting bilateral vmPFC next to TAU, in comparison with the sham condition and TAU. This study will explore the opportunities to introduce a new intervention to improve empathy, reduce violence, and reduce craving in substance-use offenders.

The present study has several strengths. First, to our knowledge only a few studies focus on increasing empathic abilities [62–67, 101] or modulate externalizing behavior [42, 68–70], but none of the studies focus on the implication of tDCS in a forensic sample. These individuals are in need of effective care, and by modulating the brain activity this can be a first step towards a new treatment program.

Second, tDCS may also influence substance abuse [49–61] and, in turn, influence the relationship between substance abuse and violent behavior. This could lead to a decrease in recidivism in forensic institutions.

Third, we will use a wide range of instruments and will gather information through multiple sources. We will obtain rsEEG, questionnaires about psychopathic traits (SRP-SF) [90], aggression (RPQ) [91], empathy (IRI) [92], alexithymia (TAS-20) [93], risky and impulsive behavior (RISQ) [99], and impulsivity (BISS11) [94]. For measuring substance abuse the study includes questionnaires that focus on alcohol use (AUDIT) [95], alcohol craving (OCDS) [96], drug use (DUDIT) [97], and drug craving (OC-DUS-version Cocaine) [98]. In addition, we have the results on the PSAP and empathy task.

Moreover, we will also include the participants who drop out during the intervention in our 5-day intervention program. This will give insight into the consequences of the formal procedures preceding the intervention and may eventually enable us to describe profiles of the intervention with tDCS in treatment success and failure.

Finally, this study will contribute to development of a cheaper and less invasive treatment for substance abuse. As mentioned before, problems that patients with substance abuse bring an enormous burden to the community (financial and safety). Previous research has found that substance abuse, especially alcohol and cocaine, are related to (violent) criminal behavior. Money invested in treatment may lead to a large reduction in the costs associated with substance abuse. Nevertheless, current interventions seem insufficient in the treatment of substance abuse in forensic mental health care and are not sufficient enough to reduce the risk of violence risk; 66% of these patients reoffend.

Despite the strengths of this current study, several limitations may threaten the quality of our study. The greatest challenge will be to have an adequate response rate at baseline and at the end of the 5-day treatment. Our target group will be conducted in a forensic institution and is participation is voluntary, so the participants can decide to quit at any time. The population has an extensive history of treatment and criminal justice, so they might have negative experiences with treatment or research studies. Moreover, the participants already have filled in numerous questionnaires in their time spent in institutions, such that they may have become tired or suspicious about the purpose of the proposed study. To keep the nonresponse rate as low as possible, the researchers conducting this study are trained to motivate and encourage the participants to complete the program. The interaction will be transparent, attentive, and flexible and the researchers will be prepared to give clear information about the purpose, goal, and aim of the current study at any time. Furthermore, a treatment that uses neurostimulation and EEG might seem scary and new to the participants as compared to TAU, so extra explanation might be needed to assure the participants that it is safe. So, to recruit as many participants as we aim to in this study will require a high degree of motivation.

Finally, an active control group (i.e. sham modulation and TAU) might lead to smaller effect sizes with active tDCS than when the tDCS treatment is compared to no treatment or a wait-list group. However, considering the seriousness of the problems of the forensic substance use offenders it would not be ethical to let them wait for an intervention and it remains important to get a sense of the effects of placebo versus the effects of active stimulation.

In conclusion, with the present study design we are able to explore what the added effectiveness is of tDCS plus TAU in comparison to sham plus TAU, which could provide valuable information for institutions, researchers, psychologists, and the professionals in the field of criminal justice. In addition, this study may help to reduce craving in forensic substance use offenders and thus reduce not only violent behavior but also recidivism. The study will contribute to knowledge about increasing empathic abilities and the functioning of the vmPFC. Specifically, this study may give insight into implementing tDCS on the vmPFC in the TAU and the setting of daily clinical practice in this complex, multiple problem target group.

## Trial status

The current study started in February 2019. The data collection will run until the 50 participants all completed the 5-day program. Follow up will be conducted after 6 months to test whether the effects of the intervention are still present. Until then, the intervention effects are unknown.

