### Procedure/design

In this double blind, placebo-controlled study, a total of 50 male participants between the age of 18 and 60 years will be randomly assigned to either the active condition or the sham condition. Eligible participants will be given written and verbal information about the study and will be invited to participate. After providing informed consent they will participate at the forensic clinic where they are admitted and all the data collected will be anonymous and linked to their participant number.

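### It is unclear whether 50 counts patients randomized or patients completing, and the stated pre-post GLM would leave out every patient without a post-test

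*Protocol article*

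**What the plan says.** All references are to the protocol article.

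- **Number randomized.** Procedure/design states that "a total of 50 male participants between the age of 18 and 60 years will be randomly assigned". The Sample section repeats 50, split 25 and 25. Power analysis says "a sample size of 50 subjects (25 per condition) is considered to have enough power to detect an effect" and states no allowance for drop-out.
- **End of data collection.** Trial status: "The data collection will run until the 50 participants all completed the 5-day program".
- **Drop-out.** The Discussion notes that participation is voluntary and says: "The greatest challenge will be to have an adequate response rate at baseline and at the end of the 5-day treatment". It also says "we will also include the participants who drop out during the intervention in our 5-day intervention program", and explains that this "may eventually enable us to describe profiles of the intervention with tDCS in treatment success and failure".
- **Analysis.** Statistical analysis plans GLMs in SPSS with arm as the between-group factor, and "the pre-post time will be included as a within-subject independent variable". This mixed design is to serve the PSAP, the empathy ratings, the questionnaires and the HKT-R.
- **Visits.** Blinding and randomization places the post-test on the Monday after the last stimulation, with a follow-up at 6 months. Primary outcomes plans to compare the 6-month PSAP and HKT-R results with those before the intervention.

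The article does not name an analysis population, does not say that drop-outs are replaced, and does not say whether a patient who stops stimulation is still assessed on the Monday or at 6 months.

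**The concern.** Two stated features pull against each other. The target of 50 is described as the number randomized in one place and, on one natural reading, as the number completing in another, while the Discussion expects losses. The chosen model then settles by default who is analysed: a patient without a post-test contributes nothing to the arm-by-time comparison, whatever the Discussion says about including drop-outs.

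The aim is a causal comparison of active with sham stimulation, and randomization supports that only for the patients as randomized. If staying to the post-test depends on arm or on response, the patients with both measurements are no longer a randomized comparison. If drop-outs were also replaced, both arms would show 25 patients and the loss would be hard to see in the results. The 6-month comparison has the same weakness and more time in which to lose patients.

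**Working it through.** **1. The plan's own figure.** Inputs from Power analysis: partial eta squared 0.25 and 0.21, power 80%, two-sided alpha 5%, 25 per arm. For two groups, d = 2 × √(η² / (1 − η²)).

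- η² = 0.25: d = 2 × √(0.25/0.75) = 1.155
- η² = 0.21: d = 2 × √(0.21/0.79) = 1.031

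With two time points, the arm-by-time test is a two-sample t-test on change scores. It needs a total of 26 (η² = 0.25) or 32 (η² = 0.21) for 80% power. The figure of 50 is therefore not reproduced from these inputs, but it is more than sufficient for them: power at 25 per arm is 0.979 and 0.947.

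**2. Do the statements fit together?** Let R be the number randomized, C the number completing and D the number dropping out, so R = C + D. Procedure/design and Sample give R = 50. Trial status, read literally, gives C = 50. The Discussion expects D > 0. All three hold only if D = 0. The article gives no drop-out rate, so the rates below are assumptions.

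| Assumed drop-out | Randomized needed for 50 completers, 50/(1 − d), rounded up | Completers if 50 are randomized |
|---|---|---|
| 10% | 56 | 45 |
| 20% | 63 | 40 |
| 30% | 72 | 35 |

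**3. What the GLM does.** The change score is post minus pre. Without a post-test it does not exist, and the patient leaves the analysis. A model with three within-subject visits would also lose anyone missing the 6-month visit. The criterion is having the assessments, not having had all ten sessions: a patient who stops on day 3 and attends on Monday stays in the pre-post GLM.

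**4. Possible size of bias (illustration).** Assume 5 of 25 in one arm (20%) leave and would have changed 1 SD less than the 20 who stay, whose mean change is m. The mean for all 25 is 0.80 × m + 0.20 × (m − 1) = m − 0.20. The patients remaining overstate that arm by 0.20 SD, which is 0.20/0.81 = 0.25 of the smallest effect that 25 per arm can detect. If the same selective loss occurs in the other arm, the difference between arms is unbiased: 0.20 − 0.20 = 0.

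**5. What it costs not to replace drop-outs.** Detectable d for a two-sample t-test on change, 80% power, two-sided 5%, equal loss in both arms:

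| Post-tests per arm | Missing | Detectable effect |
|---|---|---|
| 25 | 0% | 0.81 SD |
| 22 | 3/25 = 12% | 0.86 SD |
| 20 | 5/25 = 20% | 0.91 SD |

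At the article's own effect sizes, 20 per arm still gives power of 0.945 and 0.888, and 17 per arm gives 0.904 and 0.830. Power gives no reason to replace drop-outs.

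**The case against.** The case on the other side is substantial, and several parts of it stand.

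- **Replacement is not stated.** A reader might infer that recruitment continues until 50 have completed. Trial status speaks of data collection and of a definite group of 50, so it can equally mean that collection ends once the enrolled 50 have finished. That reading still presumes no drop-out, which the Discussion does not.
- **There is no broken promise of intention-to-treat.** A reader might take the statement on including drop-outs as such a promise. Its stated purpose is descriptive, to profile success and failure, and that can coexist with a GLM on paired data.
- **The analysed set is not declared to be those who tolerated all ten sessions.** Stopping stimulation is not the same as missing the Monday visit, and the article does not limit that visit to patients with full exposure.
- **The direction is not established.** A reader might infer bias in favour of active stimulation. The reasons for refusal given in the Discussion (past experience, fatigue, suspicion, unfamiliar equipment) are not specific to one arm, and the trial is sham-controlled and blinded.
- **A mixed model is no cure by itself.** No primary task is scheduled during the five days, so a patient who leaves before the post-test has only a baseline. No model recovers an unobserved response from that. Obtaining the post-test is what helps.
- **Some of this belongs in an analysis plan.** Analysis sets and missing-data rules are commonly left to it, and none is shown. Their absence is not the point here.

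Two points remain, and both rest on what the article does state: the counts cannot be reconciled if anyone drops out, and the chosen model excludes patients without a post-test.

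**Conclusion.** The point holds as an inconsistency together with an analysis choice that can be improved cheaply. Fifty randomized, fifty completed and drop-outs expected cannot all be true unless nobody leaves. The stated GLM would confine the efficacy comparison to patients with all the assessments it uses. That is a consequence of the model, not a declared completers-only plan.

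The size and direction of any bias are unknown. The 0.20 SD figure depends on a 20% loss in one arm and a 1 SD deficit in those lost, neither of which the article gives. It shows that selective loss could matter and does not predict that it will. Loss of power is not the issue: 50 randomized remains adequate for the article's assumed effects even with 30% missing (power 0.83 or more, at 17 per arm).

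**What to change.** 1. **Reconcile the counts** in Procedure/design, Sample, Discussion and Trial status. Either define 50 as the number randomized, with no replacement, or give separate numbers for randomized and completing and say how replacements are allocated.
2. **Seek the assessments already scheduled** (the Monday post-test and the 6-month follow-up) from every randomized patient, including those who stop stimulation, and say so in the protocol. This step does most to limit bias.
3. **Change the main model** to a linear mixed model (SPSS MIXED) with pre, post and 6 months, including all randomized patients with any outcome, by assigned arm. Patients who miss one later visit then still contribute the other.
4. **Keep the complete-case GLM** as a sensitivity analysis, and report the number and timing of losses by arm. The descriptive profiling of drop-outs can stay as planned.

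The cost is protocol wording, some effort to bring patients back for assessment, and a different procedure in the same software. Without replacement, the detectable effect rises from 0.81 SD to 0.86-0.91 SD if 12-20% of post-tests are missing.
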